### 2.10. Data Collection

All measurements will be conducted under identical conditions and by the same assessor at each time point, at a consistent time of day. Posturographic assessments (CoP displacements) for both groups will be obtained utilizing an AMTI OR67 force platform (Watertown, MA, USA). AMTI NetForce software (Watertown, MA, USA) will be utilised for the acquisition of moments and forces at a rate of 100 Hz. Data will be recorded, assigned a code, and saved on a personal computer. CoP variables will be determined using Matlab R2022 (Mathworks Inc., Natick, MA, USA).

All primary and secondary posturographic measures will be evaluated across eight distinct postural tasks, each lasting 60 s, except for the dynamic postural task which will last 30 s. The postural tasks will comprise two static conditions: (i) standing motionless with eyes open, and (ii) standing motionless with eyes closed. In addition, six dynamic conditions will be evaluated: voluntary sway in the mediolateral direction, following a metronome set at 30 Hz ((i) and (ii)) and 60 Hz ((iii) and (iv)), with eyes open and closed for each frequency. Multidirectional sway will also be assessed while playing two different videogames that challenge (v) anterior–posterior postural control (Snowboard, 30 s) and (vi) medial–lateral postural control (Penguin). It is anticipated that all assessments, including clinical evaluations, will be completed within 40 min.

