### 2.11. Data Analysis

Statistical analyses will be conducted using SPSS 20.00 for Windows. Descriptive statistics will be utilised to determine the demographic and clinical characteristics of participants in both groups (unpaired *t*-tests and χ^2^ tests). 

The normality and homogeneity of variance of all outcome measures will be assessed using the Shapiro–Wilk and Levene tests, respectively. If the assumptions of normality are met, a t-test will be employed, otherwise, the Mann–Whitney U test will be used to determine differences between the FtF and TR groups. Additionally, if the assumptions of normality are fulfilled, a repeated measures analysis of variance (RM-ANOVA) will be employed, otherwise, Friedman’s test will be used. Post hoc pairwise comparisons will be used to determine the intervention’s effect over time for each group (FtF and TR). Cohen’s d will be used to report effect sizes for the CoP variables. To allow repeated measures analysis, missing data will be adjusted by (1) replacing with the non-missing average values for each variable/week and (2) performing multiple imputations. Both methods will be used to make sure that the results are concordant. For all analyses, a *p*-value ≤ 0.05 will be considered statistically significant. All statistical analyses will be performed using IBM-SPSS 20.0 (SPSS Inc., Armonk, NY, USA).

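### Imputing missing visits so that RM-ANOVA or Friedman's test can run makes the repeated-measures result fragile; a mixed model on the observed visits avoids the step and gives one TR–FtF estimate

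*Protocol article*

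**What the plan says.** All of the analysis text is in section 2.11 (Data Analysis).

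- **Repeated-measures test.** If normality holds, "a repeated measures analysis of variance (RM-ANOVA) will be employed, otherwise, Friedman’s test will be used". Normality is judged by Shapiro–Wilk, and every analysis is decided at p ≤ 0.05.
- **Between-group test.** Under the same condition, "a t-test will be employed, otherwise, the Mann–Whitney U test will be used to determine differences between the FtF and TR groups".
- **Missing data.** The stated purpose comes first: "To allow repeated measures analysis, missing data will be adjusted by" two methods. The first is replacement by the observed mean for that variable and week.
- **Second method, and use of the two.** "performing multiple imputations. Both methods will be used to make sure that the results are concordant".

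Section 2.6 sets six assessments (baseline and weeks 2, 4, 6, 8 and 10). Section 2.3 sets 8 participants per group with 5% attrition. Section 2.1 calls the trial a non-inferiority trial.

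**The concern.** Multiple imputation produces several completed data sets. They are normally combined through an estimate and its standard error. The repeated-measures route in section 2.11 ends instead in a p-value from an omnibus test, chosen by a preliminary normality test.

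Three things follow.

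1. Friedman's test yields neither an effect estimate nor a standard error. Its chi-square, like the multi-degree-of-freedom F, can be combined only by special approximate rules.
2. The normality result can differ from one imputed set to the next. One set may then call for RM-ANOVA and another for Friedman's test.
3. The imputed answer is to be checked for agreement with the mean-replacement answer. If the imputed answer is itself unstable, the check carries little information.

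A non-inferiority comparison also needs an estimated TR–FtF difference with an interval. A Friedman p-value does not supply one, however it is pooled.

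**Working it through.** **Inputs from the article.** Difference 1.5, SD 1 cm², alpha 0.05, power 80%, attrition 5%, 8 per group (section 2.3); six visits (section 2.6); tests and threshold (section 2.11).

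**The plan's own figure.** Two-sided alpha 0.05, 80% power and a difference of 1.5 SD give 7 per group (power 80.1%). Allowing for 5% attrition, 7 / 0.95 = 7.4, rounded up to 8. The stated 8 per group is reproduced, so 8 per arm is used below.

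**How often the imputation step is needed.** The planned attrition implies 16 × 0.05 = 0.8 participants lost. If losses are independent, the chance of at least one is 1 − 0.95^16 = 1 − 0.44 = 0.56. One dropout is therefore the natural case to examine.

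**Spread of the imputed results, main check.** Assumptions: one arm of 8, six visits, normal data, within-person correlation 0.6, one person missing from week 6 on, five imputations, true change over time of 0.5–1.0 SD. For each simulated trial, count whether the five uncombined Friedman p-values lie on both sides of 0.05, and whether the Shapiro–Wilk verdict differs between imputed sets.

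| Quantity | Share of runs |
|---|---|
| Friedman p-values on both sides of 0.05 | 21–32% |
| Choice of test differs between imputed sets | 25–30% |

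The second row applies only if normality is re-tested in each imputed set. Section 2.11 does not say whether it is.

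**Same question under other assumptions.** With all 16 people in one Friedman test, correlation 0.5 and 20 imputations, the p-values straddled 0.05 in 8%, 14% and 20% of 400 runs with 1, 2 and 3 dropouts. The size depends on the set-up, but the spread is present in each.

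**Can the results be pooled?** In that second set-up the Friedman statistics were also combined by the D2 rule for chi-square statistics. Every run gave one finite pooled p-value. In one run with two dropouts, the 20 Friedman p-values ranged from 0.27 to 0.69 and the pooled value was 0.43. So a single answer can be obtained. Two limits remain: D2 rests on a chi-square approximation that is rough with 8 per arm, and it does not combine an F from some sets with a Friedman chi-square from others.

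**The case against.** The strongest reply is that the article is only being brief. It says that multiple imputation will be done, not that results will be left uncombined. The pooling rule, the number of imputations and the imputation model are details that an article leaves to the full protocol or SAP. Straddling p-values are ordinary between-imputation variation, which pooling exists to absorb. And replacing RM-ANOVA by a mixed model is partly a matter of preference, with a real drawback for bounded scales such as the Barthel Index and Tinetti's scale.

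Much of this stands. Several stronger readings are tempting, and the document does not support them.

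- **That no valid pooling method exists, or that there is no single imputed answer.** This is not so. The t-test and mean contrasts pool by Rubin's rules, and F and chi-square statistics pool by D1- or D2-type rules.
- **That the unstated pooling rule is itself an error.** On its own it is missing detail, and no finding.
- **That imputed data will feed the Mann–Whitney test.** The stated purpose is the repeated-measures analysis, so this is an inference. No Mann–Whitney figures are counted here.
- **That one imputation model must cover everything.** Five CoP measures × 8 tasks × 6 visits = 240, plus 4 clinical measures × 6 visits = 24, gives 264 values per person. No joint model for these is proposed, and imputing each outcome and task separately is compatible with the text.
- **That about 26% of people will be incomplete.** That is 1 − 0.95^6, which takes 5% as the rate of independently missed visits. The article gives 5% as attrition.

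What remains is the pairing that the article does state: imputation done in order to run an omnibus F or a rank test, with the choice between them set by the data.

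**Conclusion.** The concern holds in a limited form. The multiple-imputation leg is a poor match for the RM-ANOVA-or-Friedman route, and its result is fragile even with one dropout. Under the assumptions shown, uncombined Friedman p-values disagreed about significance in roughly 8–32% of runs with one dropout. The test itself changed between imputed sets in 25–30%, if normality is re-tested in each. Pooling reduces the first problem at the price of a rough approximation. It does not resolve the second.

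This does not invalidate the trial. It is an inexpensive improvement worth making, because a better method uses data already planned for collection and delivers the estimate and interval that a non-inferiority comparison needs.

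**What to change.** For the repeated-measures analysis of the CoP outcomes, replace imputation followed by RM-ANOVA or Friedman's test with a linear mixed model fitted to all observed visits. Suggested content:

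- fixed effects for arm, visit, arm-by-visit and the baseline value (so the modelled visits are weeks 2, 4, 6, 8 and 10);
- a random participant intercept;
- small-sample degrees of freedom;
- as the reported result, the week-6 TR–FtF difference with its confidence interval.

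A participant with some post-baseline visits missing still contributes the others, so no imputation is needed for this analysis.

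If multiple imputation is kept as a sensitivity analysis, impute each outcome and task from its own visits with arm in the model. Pool only the week-6 difference and its standard error.

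**Cost.** New wording and a change of procedure in section 2.11; no extra data or participants. The model assumes roughly normal residuals, and with 16 people it can support only a simple covariance structure. The bounded clinical scales may need separate handling.

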### 2.12. Data Monitoring

Continuous monitoring will be conducted by the clinical team, overseen by the research team and the Ethics Committee of the University of Talca. In the event of any adverse events, the Ethics Committee of the University of Talca will be immediately notified to determine if any modifications or termination of the trial are necessary.

### 2.13. Patient and Public Involvement

No patients will be involved in the design of the trial.

### 2.14. Ethics

The trial is in accordance with the Declaration of Helsinki and adheres to the Chilean laws regarding the rights and obligations of patients and research involving human subjects. Ethical approval for the trial was granted by the Ethics Committee of the University of Talca (Ref. No. 24-2018). This protocol was registered with the Australian and New Zealand Clinical Trials Registry (ACTRN12621001380886). Written informed consent will be obtained from all participants.

## 3. Discussion

Anticipated findings from this trial suggest that the TR modality will exhibit non-inferior effectiveness to the FtF modality, as evaluated through clinical and posturographic assessments. This expectation draws support from preliminary evidence surrounding the implementation of TR and VR interventions in different settings. According to a recent systematic review, telemonitoring and telerehabilitation were the most used methods of telecare interventions in older populations. The findings from various studies indicated that these interventions had a positive impact on different dimensions of quality of life, particularly in older adults. Evaluating the impact of telecare interventions can provide valuable insights for system developers to improve the effectiveness of current and future telecare technologies to better meet the needs of users, particularly older adults. Future research can focus on evaluating the impact of specific telecare systems on targeted populations using diverse research methodologies. This can help in understanding the effectiveness of telecare interventions in different settings and for different populations and guide the development and implementation of telecare technologies that are tailored to specific user requirements [51]. Similarly, telehealth occupational therapy has been widely utilised for older adults, with a focus on providing convenient occupational assessment and intervention for both occupational therapists and their elderly clients. Telehealth occupational therapy also allows for monitoring of patients’ activities and provides rehabilitation counselling and health education to older adults and their caregivers, resulting in improved home life security and efficacy of occupational therapy interventions. Particularly during the COVID-19 pandemic, telehealth has emerged as a valuable alternative to face-to-face modalities, ensuring continuity of care while minimizing risks of infection [52].

The feasibility and efficacy of telerehabilitation programs seems to be comparable to conventional physiotherapy in terms of functionality level and quality of life, but the evidence is limited to a small corpus of studies. Telerehabilitation has been shown to achieve high levels of patient satisfaction and adherence, with values like those of traditional face-to-face/in-person rehabilitation methods. This suggests that telerehabilitation can be a viable and effective alternative for delivering rehabilitation interventions, with outcomes to comparable those of conventional in-person physiotherapy [53]. 

In the last three years, research on telerehabilitation has risen not only because of the technological improvements and population aging, but also to address rehabilitation needs during lockdowns and to treat post-COVID syndromes as Long COVID [54]. During the COVID-19 pandemic, telerehabilitation has predominantly relied on video and audio calls, utilizing widely accessible technologies and free videoconferencing tools. Based on existing evidence, telerehabilitation is considered feasible and effective in maintaining rehabilitation continuity while minimizing the risk of infection and travel burden during pandemics. However, despite its potential benefits, telerehabilitation is not yet widely utilised in clinical settings, and conclusive findings are currently limited. Nevertheless, telerehabilitation appears to be a viable and safe option for remote delivery of rehabilitation services using readily available mobile technologies, enabling continued care while adhering to social distancing measures imposed by pandemics [55].

Recent research like this trial has found that telerehabilitation, specifically a home-exercise program supervised by physical therapists, has the potential to be as effective as supervised rehabilitation in improving functional outcomes in female patients with patellofemoral pain syndrome [56]. In the case of Long COVID, a virtual rehabilitation programme was highly valued by participants, as the digital delivery enabled self-management of their rehabilitation process. However, there were some barriers to attendance, including challenges related to work/life balance, use of technology, and health inequalities. Additionally, Long COVID, a condition affecting some individuals recovering from COVID-19, was poorly understood by employers, which may have posed challenges for participants in the programme. Overall, despite the positive feedback and benefits of the virtual rehabilitation programme, these barriers and challenges highlight the need for further considerations and support to ensure optimal participation and outcomes for individuals with Long COVID [57]. In a sample of 32 patients with Long COVID, a statistically significant improvement was observed after a 4-week digital physiotherapy practice intervention with an individualised and customised exercise program. The improvement was accompanied by a small to medium effect size, high adherence rates, and values above the minimal clinically important difference. This suggests that the intervention was effective in improving outcomes in this population. However, it is important to note that this conclusion is based on a sample of 32 patients, and further research is needed to validate these findings in larger and more diverse populations [58].

In the case of telerehabilitation focused on older patients, several systems and programmes have been developed over the last years, including some using VR solutions. For example, the use of Virtual Reality Comprehensive Rehabilitation Rooms (VRCRR) in physiotherapeutic treatment for older adults living in a community has been shown to significantly improve their functional performance, particularly in terms of static balance. This innovative approach, using VR technology, offers a viable alternative to traditional physiotherapy methods for enhancing individual functional performance. The self-designed VRCRR solution allows for a tailored physiotherapy programme to be pursued in the comfort of one’s own home environment, making it a promising option for improving physical function in older adults. Therefore, VR technology can be used effectively in physiotherapy management to enhance individual functional performance, especially in terms of static balance, and can be conveniently used at home through a self-designed VRCRR solution. Overall, this suggests that VR can play a valuable role in the rehabilitation of older adults in the community setting [59]. Furthermore, for geriatric patients who have undergone total hip replacement (THR) following a hip fracture, the use of an Internet-based rehabilitation management system has shown to have multiple benefits. Not only does it promote physical rehabilitation, it also plays a positive role in psychological rehabilitation and prevention of complications. This innovative approach offers new ideas and methods for clinical rehabilitation, providing a holistic approach to improve overall patient outcomes. The integration of technology into geriatric rehabilitation can greatly enhance the effectiveness and efficiency of the rehabilitation process, benefiting both the physical and psychological wellbeing of patients recovering from hip fractures and THR. This highlights the potential of Internet-based rehabilitation management systems as a valuable tool in the geriatric rehabilitation field [60].

Moreover, telerehabilitation could be used in frail or cognitively impaired older patients. Telerehabilitation has shown promise in improving the quality of life for older patients with mild cognitive impairment or cognitive frailty, and it can serve as a useful and supportive digital platform for healthcare. Commonly used technologies for telerehabilitation include smartphones or telephones with Internet, television-based assistive integrated technology, mobile applications, and video conferencing. Despite its potential, the utilization of telerehabilitation in managing cognitive frailty among older adults is still limited, and further research is needed to evaluate its feasibility and acceptability. Although telerehabilitation has been implemented among older adults with mild cognitive impairment or cognitive frailty, social support is still necessary to improve adherence and effectiveness. Future research should focus on evaluating the acceptance and existing knowledge of participants towards telerehabilitation to better achieve its intended outcomes. By understanding the perceptions and attitudes of older adults towards telerehabilitation, interventions can be tailored to address potential barriers and enhance acceptance. Additionally, further research can explore the role of social support in facilitating the implementation and effectiveness of telerehabilitation in older adults with cognitive frailty. This can include strategies to provide adequate support, such as caregiver involvement, community resources, and technological assistance, to overcome challenges and ensure successful telerehabilitation outcomes. Overall, continued research and evaluation of telerehabilitation in older adults with cognitive impairments can contribute to optimizing its use as an effective and feasible approach for improving their health and wellbeing [61]. The utilization of cutting-edge exercise equipment designed for rehabilitating frail older adults, in combination with a structured exercise regimen and the incorporation of VR solutions, has demonstrated clear effectiveness. As a result, patients have been able to transition from frailty to pre-frailty stages while experiencing notable improvements in motor and cognitive functions. The integration of modern technology, particularly VR technology, as part of rehabilitation management for older adults with frailty syndrome has proven to be a successful complement to conventional methods. The versatility of VR technology solutions, including their adaptation for home use with remote supervision, has made this innovative rehabilitation approach more appealing to patients, who find it engaging and mentally stimulating. The significant potential of this approach lies in its ability to achieve desirable therapeutic outcomes with enhanced effectiveness [62]. The prospect of incorporating frail older adults into telerehabilitation programs, as outlined in the protocol described herein, represents a significant stride towards extending rehabilitation services to areas where they are most needed. By leveraging telecommunication technologies to deliver rehabilitation interventions remotely, this approach has the potential to overcome geographical and logistical barriers that often limit access to rehabilitation services for older adults in underserved or remote regions. This expansion of rehabilitation coverage to vulnerable populations, such as frail older adults, through telerehabilitation programs has significant implications for addressing healthcare disparities and improving access to care. The integration of telehealth technologies in rehabilitation can facilitate the delivery of tailored interventions, monitoring, and support to individuals in their own homes or local communities, regardless of their geographical location, socioeconomic status, or mental capacity.

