## Abstract

**Background:** Several exercise methods with virtual reality devices have been used in treatments for older adults and patients with neurodegenerative diseases, although the mechanisms continue to be elucidated. The aim of this study is to establish the feasibility and effectiveness of a rehabilitation programme using low-cost virtual reality aimed at improving postural balance in older adults. It also seeks to compare low-cost virtual reality under two delivery modalities, telerehabilitation (TR) in elderly centres and face-to-face (FtF) in rehabilitation centres. **Methods:** The study is set up as a non-inferiority two-arm parallel triple-blind randomised controlled clinical trial. Sixteen persons aged 65 to 75-years-old will be included. Eighteen Wii therapy sessions (25–30 min) will be provided through both FtF (control group, *n* = 8) and TR (exposure group, *n* = 8), both with a Nintendo Wii balance board. Data will be collected at baseline (week 0), during the Wii therapy sessions (weeks 2, 4, and 6), and during the follow-up (weeks 8 and 10). The primary outcome will be the area of centre-of-pressure (CoP) sway; secondary outcomes will be medial–lateral and anterior–posterior velocity and standard deviation of CoP; and tertiary outcomes will be clinical measures: single-leg stand, timed up-and-go tests, Barthel Index, and Tinetti’s scale. Statistical analyses will be performed using SPSS 20.00 for Windows. The trial adheres to the Declaration of Helsinki and the Chilean laws of rights and duties of the patient and research in humans. Ethical approval was obtained from the Ethics Committee of the University of Talca. Written informed consent will be obtained from participants. **Discussion:** In this trial, older adults from a Chilean city with a large rural and underserved population share will be included to test the feasibility and effectiveness of a rehabilitation programme using low-cost VR aimed at improving postural balance to generate evidence to support decision makers generating public health policy. **Trial registration:** Australian New Zeeland Clinical Trials Registration (ACTRN12621001380886).

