#### 2.6.2. Secondary Outcome

As for the secondary outcome measures derived from the posturographic evaluations, the standard deviation and velocity of the CoP along the medial–lateral and anterior–posterior axes will be employed. The CoP standard deviation indicates the extent of variation in CoP displacements, while CoP velocity serves as an indicator of the capacity to adapt to postural changes, where higher values are indicative of suboptimal balance control. This is because delayed postural adjustments result in significant CoP displacement, necessitating swift corrections to ensure stability [40].

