#### 2.6.3. Clinical Measurements Outcome

This study will use the Tinetti, single-leg stance, and timed up-and-go tests and the Barthel Index as clinical measurements, as described in a recent clinical trial [49]. It is interesting to note that these measures cannot identify fallers in the older adult population but are useful for identifying and tracking balance impairment in this population [50].

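### The ranking of outcomes plays no part in error control or in the TR versus FtF conclusion: one unadjusted 0.05 rule covers all analyses, and the evaluation is not limited to the primary outcome

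*Protocol article*

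**What the plan says.** The Abstract ranks the outcomes. It states that "The primary outcome will be the area of centre-of-pressure (CoP) sway", places the CoP velocity and standard deviation second, and adds that "tertiary outcomes will be clinical measures: single-leg stand, timed up-and-go tests, Barthel Index, and Tinetti’s scale".

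Section 2.6.2 defines four secondary variables: "the standard deviation and velocity of the CoP along the medial–lateral and anterior–posterior axes will be employed". Section 2.6.3 lists four clinical tests: "This study will use the Tinetti, single-leg stance, and timed up-and-go tests and the Barthel Index as clinical measurements". Section 2.10 multiplies the posturographic part: "All primary and secondary posturographic measures will be evaluated across eight distinct postural tasks". Section 2.6 schedules a baseline assessment and five later ones (weeks 2, 4, 6, 8 and 10).

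Section 2.11 plans a t-test or Mann–Whitney test between groups, repeated measures ANOVA or Friedman's test over time, and post hoc pairwise comparisons. It then sets one rule: "For all analyses, a *p*-value ≤ 0.05 will be considered statistically significant".

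The opening sentence of the Discussion expects that the "TR modality will exhibit non-inferior effectiveness to the FtF modality, as evaluated through clinical and posturographic assessments". Section 2.6 is equally broad: it says that both kinds of measure will be used to assess how the effects of the two groups differ.

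**The concern.** A ranking of outcomes matters only if it changes something: which result decides the question, which results are tested at full alpha, or how mixed results are read. Here it changes none of these. The threshold is the same for every outcome, and neither Methods nor Discussion limits the TR versus FtF evaluation to CoP area.

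Two things are at stake. First, with several outcomes each tested at 0.05, a chance difference can appear when the two modalities are equivalent, and a chance difference against TR would then count as evidence against it. Second, if the results are mixed, the text allows the conclusion to be supported by whichever measures look favourable. With 8 per arm, this could include citing non-significant results as agreement. The article intends the result to inform public health policy, so the reader needs to know beforehand which outcome carries it.

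**Working it through.** **The plan's own figure.** Section 2.3 gives a difference of 1.5 units, SD 1 cm², alpha 0.05, power 80% and 5% attrition. Taking a two-sided test and the normal approximation:

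n = 2 × (1.96 + 0.84)² × 1² / 1.5² = 6.98, so 7 per group; 7 / 0.95 = 7.4, so 8 per group.

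This reproduces the stated 8 per group (16 in total). It is sized for one comparison at alpha 0.05.

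**Number of tests outside the primary outcome.**
- One test per variable: 4 secondary + 4 clinical = 8.
- Every task tested at one visit: 4 × 8 + 4 = 36.
- Every task at all five post-baseline visits: 36 × 5 = 180.
- The four clinical tests alone at one visit: 4.

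**Independent tests, no true difference.** The chance of at least one p ≤ 0.05 is 1 − 0.95^k:
- k = 4: 18.5%
- k = 8: 33.7%
- k = 36: 84.2%
- k = 180: above 99.9%

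The expected number of false differences is 0.05 × k: 0.4 for k = 8, 1.8 for k = 36 and 9 for k = 180.

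**Correlated tests.** The article gives no correlations, so a range is assumed. The simulation used normal outcomes with a common correlation rho, 8 per arm, identical arms and two-sample t-tests at two-sided 0.05.

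| Tests | rho 0 | rho 0.5 | rho 0.8 | rho 0.9 |
|---|---|---|---|---|
| 4 (clinical only) | 19% | 16% | 12% | 10% |
| 8 (one per variable) | 34% | 26% | 16% | 12% |
| 36 (all tasks, one visit) | 84% | 57% | 29% | 19% |
| 180 (all tasks, five visits) | >99.9% | 90% | 45% | 27% |

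**Direction.** By symmetry, half of the expected false differences go against TR. For 36 independent tests, the chance of at least one adverse to TR is 1 − 0.975^36 = 60%. In the simulation it is about 30% at rho 0.5 and 15% at rho 0.8.

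**The case against.** The Discussion sentence is a forecast introducing a literature review, not a decision rule. A reader might infer from it that secondary and clinical outcomes formally carry the non-inferiority conclusion; the article does not say so. What remains is that Section 2.6 describes the evaluation just as broadly in Methods, and nothing narrows it.

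An outcome ranking exists, so it would be wrong to say that there is no hierarchy. Further detail, such as a testing order or an exploratory label, could sit in a full protocol or analysis plan that is not shown. That answers a complaint about omissions. It does not answer the rule that the article does state: 0.05 for all analyses. An analysis plan that restricted inference to CoP area would depart from this published text.

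The count of 180 is a worst case. Section 2.3 ties the comparison to six weeks, and Section 2.11 includes repeated measures methods, so a separate between-arm test at every visit is not specified. The objection stands, and 180 should be read as an upper bound.

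The simulated error is not the error of a non-inferiority claim. With identical arms non-inferiority is true. If success were required on every outcome jointly, the type I error would not be inflated. This also stands: the figures describe false differences only.

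Finally, measures taken from the same recordings may be strongly correlated. At rho 0.8 or above a false difference is less likely than not, even with 180 tests.

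**Conclusion.** The point holds as one about a stated rule and its scope. Section 2.11 applies an unadjusted 0.05 to all analyses, and Section 2.6 and the Discussion do not limit the TR versus FtF evaluation to the primary outcome. The ranking therefore has no role in error control or in the conclusion.

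For one visit, with identical arms and 8 per group, the chance of at least one false difference among the secondary and clinical outcomes is about 12% to 34% for 8 tests and 19% to 84% for 36 tests. Each exceeds 5%, but the ranges rest on assumed correlations from 0.9 to 0 and on how many tasks are tested.

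A reader might infer that chance differences are likely. The documents do not support that across the range: it holds with all tasks counted at moderate correlation, and fails at high correlation or with 8 tests. Nor do the figures give a false non-inferiority rate. The risk of selective citation is separate and has not been quantified.

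**What to change.** - In Section 2.11, state that the TR versus FtF conclusion rests only on the primary outcome: CoP area at one named postural task, at week 6. Naming the task is necessary because CoP area is itself measured on eight tasks at five post-baseline visits, so the words primary outcome alone do not identify a single comparison.
- Confine the 0.05 decision rule to that comparison.
- Report the secondary CoP variables and the four clinical tests as supportive, as between-group differences with 95% confidence intervals, with no stand-alone non-inferiority or superiority claim.
- Reword the opening sentence of the Discussion to match.

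This needs wording only, with no new data or participants. The cost is that the secondary and clinical outcomes can no longer carry a claim of their own.
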